## **2.2 STUDY DESIGN**

### **2.2.a RANDOMIZED CONTROLLED TRIAL STUDY**

The IMPACT study will implement a three-arm randomized controlled trial (RCT). Of the three study arms, two will be experimental groups with structured exercise sessions (once-weekly or thrice-weekly) as the designed intervention. The remaining study arm will serve as the control group. The study randomization software will assign each eligible study participant into one of three study arms.

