#### **Arm 3: Usual Care (Control Group)**

The third arm of the IMPACT study does not required study participants to attend any group exercise sessions. Study participants are to continue with current T2DM management and seek care from their personal healthcare provider. Study participants within this study arm are expected to attend a total of six study visits.

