## **Chapter 6: Randomization and Data Analysis Plan**

## 6.1 RANDOMIZATION

### 6.1.a RANDOMIZATION

Block Randomization is the method to be used to randomize study participants into study arms. The method is developed to pre-specify the number of arm assignments in a random order. IMPACT will utilize Block Randomization in conjunction with stratification in order to promote balance of participant characteristics within each study arm. The participant characteristics, or parameters, to be used for the IMPACT study includes: (1) age, (2) gender, and (3) HbA1c level.

Participant characteristics will be stratified as followed:

- Age (years)
  - >29.9 – 50.9 (young age)
  - 51.0 – 65.0 (older age)
- Gender
  - Male
  - Female
- HbA1c (percentage)
  - 6.6 – 7.9 (low A1c)
  - 8.00 – 9.9 (high A1c)

As a result, there are eight (8) strata in total:

1. Low HbA1c, younger age and female
2. Low HbA1c, younger age and male
3. Low HbA1c, older age and female
4. Low HbA1c, older age and male
5. High HbA1c, younger age and female
6. High HbA1c, younger age and male
7. High HbA1c, older age and female
8. High HbA1c, older age and male

Each block size will contain six (6) group assignments, evenly distributed across the three study arms. The blocks will contain random permutations (ie. 211332, 321231, etc) that are pre-determined by SAS.

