### **Primary Outcomes and Process Measures**

Primary outcomes and process measures will be compared between the three intervention arms (weekly, thrice-weekly, usual care). Primary outcomes include absolute change in percent HbA1c, and process measures include change in VO2 max and self-reported physical activity. Adherence will be defined as attending more than 80% of assigned structured exercise sessions, and will be used as a covariate for stratification or adjustment.

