### **STUDY AIM 3: COST EFFECTIVENESS**

#### **Research Questions**

1. What is the most cost-effective frequency of PAD-SMAs based on percentage lowering of HbA1c?
2. What is the most cost-effective frequency of PAD-SMA sessions based on quality of life?

The average cost and outcomes of each intervention arm and the usual care arm will be first assessed. Using each cost and effectiveness measure, cost-effectiveness of the three levels of interventions will be computed in comparison to the usual care group.

Cost-effectiveness will be assessed with two indices: (1) average cost-effectiveness for each intervention and control group, defined as  $(\text{total costs})_A / (\text{average effectiveness})_A$  for group A, and (2) incremental cost-effectiveness ratio (ICER) of groups A vs. B, defined as  $\{(\text{total cost})_A - (\text{total cost})_B\} / \{(\text{effectiveness})_A - (\text{effectiveness})_B\}$ . The ICER indicates the expected incremental cost of each intervention arm over no intervention per unit improvement in effectiveness.

Confidence intervals with bootstrapping standard errors will be used to elicit statistical inferences of each index. The indices using varying costing and effectiveness metrics will be compared. By study design, significant differences across the three intervention arms in patient demographic (age, gender, race/ethnicity), clinical (co-morbidities) or behavioral (i.e. adherence) characteristics are not expected. However, if systematic difference in patient characteristics between intervention and usual care group is detected, alternative models specifically adjusting for selection issues will be employed, such as propensity score matching and selection models. Furthermore, heterogeneous treatment effects with subgroup analysis

based on patient gender, age, and baseline clinical conditions (in BMI, HbA1c levels) will be explicitly examined.

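### The Aim 3 cost-effectiveness method is chosen by observed imbalance between randomised arms, with no sensitivity label and no limit to baseline variables

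*Protocol*

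**What the plan says.** Protocol 6.2.a, Study Aim 3, first sets out average cost-effectiveness for each group and incremental ratios between groups, with bootstrap intervals. It then says that, by design, "significant differences across the three intervention arms in patient demographic (age, gender, race/ethnicity), clinical (co-morbidities) or behavioral (i.e. adherence) characteristics are not expected". The next sentence gives the exception: "if systematic difference in patient characteristics between intervention and usual care group is detected", then "alternative models specifically adjusting for selection issues will be employed, such as propensity score matching and selection models". The section does not say how a difference is to be detected, which variables count, or whether the alternative models stand beside the incremental ratio or supersede it.

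Four other places bear on this:

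- Section 2.2.a describes a three-arm randomised trial, and 6.1.a stratifies by age, gender and HbA1c: "Each block size will contain six (6) group assignments, evenly distributed across the three study arms".
- Section 6.2.a, Study Aim 1, Primary Outcomes and Process Measures: "Adherence will be defined as attending more than 80% of assigned structured exercise sessions".
- Section 2.2.a, Arm 3: usual care "does not required study participants to attend any group exercise sessions".
- Section 6.2.a, Study Aim 1, Statistical Analysis, keeps patients in their randomised arm and places re-analysis by actual attendance expressly among the sensitivity analyses. Aim 3 has no such label.

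**The concern.** Propensity matching and selection models address non-random entry into treatment groups. Here a random sequence assigns the arm, so among all randomised patients a baseline difference is chance and there is no selection into arm to model. A rule that looks at the imbalance and then changes the method makes the estimator depend on the data, and its error properties are no longer those of either method alone. One of the two named methods, matching, also removes randomised patients who have no close match.

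Listing adherence beside age, gender, race/ethnicity and co-morbidities adds a second difficulty, because it treats something that happens after allocation as if it were a baseline characteristic.

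Section 6.2.b counts cost-effectiveness among the primary analyses. It gives Aim 3 no sample size of its own and relies on the numbers for Aims 1 and 2, so a step that sheds patients draws on a sample not planned for it.

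**Working it through.** The Aim 3 text contains no figure to reproduce. The sample size context checks: 92 / (1 - 0.20) = 115 per arm, and 3 x 115 = 345, as stated in 6.2.b.

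**1. Chance of a false trigger.** Under correct randomisation, with k independent characteristics each tested at level a, the chance of at least one detected difference is 1 - (1 - a)^k. The protocol states neither k nor a test for this step. The level a = 0.01 is taken from the general significance rule in 6.2.a.

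- k = 4 (age, gender, race/ethnicity and co-morbidities, the baseline items the sentence names): 1 - 0.99^4 = 0.039, about 4%.
- k = 8 (assumed): 1 - 0.99^8 = 0.077, about 8%.
- k = 2 (only the two named items that are not stratification factors): 1 - 0.99^2 = 0.020, about 2%.

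Stratified blocks hold age and gender close to balance, so the figure for k = 4 is if anything high.

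**2. Patients lost to matching.** Two simulations applied propensity matching within a caliper of 0.2 SD to correctly randomised arms. The covariates and caliper are assumptions; the protocol gives neither.

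| Covariates | Per arm | Mean share unmatched | 5th to 95th percentile |
|---|---|---|---|
| 5 | 92 | 19% | 13-25% |
| 5 | 115 | 18% | 12-24% |
| 8 | 92 | 22% (78% of pairs kept) | not recorded |

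In the 8-covariate case (R-squared 0.25, 2,000 replicates), the SD of the estimate was 0.142 after matching and 0.125 with covariate adjustment on all patients. The variance ratio is (0.142 / 0.125)^2 = 1.29. In precision, 92 matched-from patients per arm are then worth about 92 / 1.29 = 71 analysed by regression.

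**3. Adherence.** Set side by side, the passages do not fit:

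- Adherence is attendance at assigned sessions, so it is observed only after allocation.
- Usual care has no assigned sessions, so the quantity does not exist in Arm 3.
- The Aim 3 sentence nevertheless includes it among characteristics expected not to differ across all three arms.

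**The case against.** The other side has several sound points.

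- **The incremental ratio is not said to be dropped.** A reader might infer that the switched analysis replaces the randomised comparison. The text says only that alternative models will be used, after average costs and outcomes have been assessed by arm. What stands is that their status is left open.
- **Adherence cannot be matched against usual care.** A reader might infer that matching on adherence would bias the comparison, or that a gap in adherence between the once- and thrice-weekly arms would almost always set off the rule. Neither follows. The trigger compares intervention with usual care, not Arm 1 with Arm 2, and its own sentence speaks only of patient characteristics. A variable undefined in one group cannot be compared or matched with that group.
- **A high false-trigger rate is not supported.** Eight tests at 5% would give 1 - 0.95^8 = 34%, but the protocol states no number of tests and sets P<0.01.
- **Selection models keep all patients,** and both methods are given as examples, so regression on everyone is not excluded.
- **Selective loss is possible.** Section 6.2.b allows for 20% attrition, and 6.2.a treats patients who leave their assigned frequency as lost to follow-up and uses only their on-protocol data. The groups actually analysed could therefore differ for reasons other than chance, and selection models are a recognised tool for that.

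The last point justifies keeping these methods in a sensitivity role. It does not justify the rule as written. Aim 3 does not mention dropout, and observed differences in patient characteristics are what set it off.

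**Conclusion.** The point holds and is confined to Aim 3; the HbA1c analysis under Aim 1 is not affected. The protocol lets an undefined finding of imbalance select the cost-effectiveness estimator in a stratified randomised trial. It does not restrict the covariates to baseline variables or mark the alternative as a sensitivity analysis.

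The sizes are modest and conditional. If matching were chosen, about 18-22% of patients would be lost under the assumed covariates and caliper. The false-trigger rate would be about 4% to 8% at P<0.01 for 4 to 8 independent characteristics. Neither range comes from a protocol figure. The argument for change does not depend on them: an analysis fixed in advance on all randomised patients avoids the problem whatever the true rates. The listing of adherence is a plain inconsistency with the protocol's own definition and with the content of the usual care arm. The documents do not show that it would bias the result.

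**What to change.** In 6.2.a, Study Aim 3:

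1. Make the main analysis one pre-specified as-randomised comparison of cost and effect (or of net benefit). Adjust it by regression for the stratification factors (age, gender, baseline HbA1c) and the baseline value of the effect measure, regardless of observed imbalance.
2. Remove adherence from the list of characteristics expected to be balanced, and keep it out of the adjustment.
3. Keep propensity matching and selection models only as labelled sensitivity analyses (for example, for selective dropout), or for comparisons with nonparticipants, who were not randomised.

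Age, gender, HbA1c and SF-12 are already collected at baseline under 4.1.b, so no new data or patients are needed. The cost is a wording change and slight extra analysis work.

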## **STUDY RECRUITMENT ANALYSIS**

Analyses related to study recruitment will be performed. Methods of participant recruitment, electronic versus postal mail recruitment, will be summarized and compared. Participant response rates according to the individual recruitment methods will also be determined.

Simple analyses will also be conducted to summarize the amount of effort in participant recruitment. This will include tabulating the number of calls made to potential participants, the number of voice messages left on voicemail boxes, the total amount of time for all phone screens and the average amount of time for a single phone screen. In addition, the frequency and percentage of various phone screening outcomes: (1) Completed, (2) Incomplete, (3) Not Interested, and (4) Lost to Follow-Up, will be examined.

## **6.2.b POWER AND SAMPLE SIZE**

The primary analyses for this study will be comparing the clinical outcomes, patient-centered outcomes, and cost effectiveness of structured exercise regimens across varying frequencies (once vs. thrice-weekly, compared to usual care). For Specific Aim 1, overall change in baseline of outcome values will be examined (e.g. HbA1c, VO2max, physical activity). By the algebraic properties of log and variance, we estimated difference in groups as  $\log(\text{HbA1c}_1) - \log(\text{HbA1c}_2) = \log(\text{HbA1c}_1 / \text{HbA1c}_2)$ , and  $\text{SD}(\log(\text{HbA1c})) = \text{SD}(\text{HbA1c}) / \text{mean}(\text{HbA1c})$ . A two-sample *t*-test between means, Bonferroni adjusted  $\alpha = 0.05/3 = 0.016$ , assuming normality of  $\log(\text{HbA1c})$ , equal group variances, and a baseline mean HbA1c of 6.5%, we will have 80% power to detect a 0.5% point difference in HbA1c with 92 patients/arm. Accounting for a 20% attrition, this will require 115/arm, 345 patients total.

Specific Aim 2 seeks to compare the satisfaction of patients between groups as measured by self-reported satisfaction questionnaires. The data will be collected using ordered, multi-point Likert scales, and in some cases responses will be dichotomized (e.g. 5 points with 1-3 vs 4-5). For a power/sample size estimate, we used a difference in proportion estimate. Using a likelihood ratio, chi-squared test of two proportions,  $\alpha = 0.05/3 = 0.016$ , power=0.80 and an underlying referent satisfaction of 80% and equal sample sizes of 92-115/arm per above, we are able to detect minimum differences in proportions of 15 percentage points, and minimum detectable odds ratios 4.9. To compare the quality of life metrics of patients between groups as measured by SF-12,® the data will be collected using SF-12® and appropriately converted to a bounded value between 0 and 1. In analyses, we will use the inverse normal transformation of quality of life to obtain a normally distributed quality of life value. For a power/sample size estimate, we estimated the difference in score, using a two-sample *t* test with pool variance of 0.09, the Delta Method and Taylor Series expansion, properties of the inverse normal transformation,  $\alpha = 0.05/3 = 0.016$ , power=0.80, and equal sample sizes of 92-115/arm per above. We are able to detect a minimum difference in quality of life scores of 0.09 (e.g. 0.50 vs 0.59 would be detectable, on a scale from 0-1).

Cost-effectiveness (Specific Aim 3) analyses use aggregate cost and effectiveness values, along with confidence intervals derived from a bootstrap method. Therefore, sample size meeting the criteria for the above two aims would be sufficient for Specific Aim 3. Missing data will be mitigated through retention strategies (see Section C.8) and augmentation with EHR data (see Section C.5.3). For patients missing some, but not all, follow-up data, the missing data mechanism will be explored and modern imputation methods such as multiple imputations will be used to impute missing covariates following satisfaction of the method's assumptions.

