### **Statistical Analysis**

In univariate analyses, the percent change from baseline will be compared across intervention arms using appropriate parametric (ANOVA, *t* tests) or non-parametric (Wilcoxon) methods.

In multivariate analyses, change in outcomes will be modeled using linear regression. Percent change from baseline will be a continuous outcome with intervention arm as the predictor of interest and various participant characteristics as covariates (e.g. sex, age, race/ethnicity, anthropometry, self-reported diet and exercise, pharmacotherapy, family history, etc.). Repeated measures analysis using the outcome at different time points and mixed-effects models will also be performed. Available nonparticipants will serve as contemporaneous comparators to address possible secular trends in outcome values.

Study participants in the exercise program may also be undergoing concomitant pharmaceutical therapy to reduce HbA1c. The approach is to repeat the above analyses stratified by use of hypoglycemic medication. Another approach is to use a composite binary outcome variable for whether participants were successful in either decreasing diabetes medication or reduced HbA1c by 0.5% without increasing medications. Logistic regression will be used to assess the likelihood of achieving the composite outcome.

Study participants will be studied based on their randomized assignment (intention-to-treat). In sensitivity analyses, participants may be re-analyzed based on actualized attendance if they more closely resemble one of the other arms (once-weekly, thrice-weekly, usual care). A study participant assigned to thrice-weekly, who attends only once a week may be re-analyzed as a weekly patient. Stratification by adherent (attendance >80%) or not will also be another sensitivity analysis.

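### With exactly three arms, Bonferroni 0.05/3 on the HbA1c contrasts is valid but costs power that a closed procedure such as Shaffer's step-down would keep at the same N and the same 5% family error

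*Protocol*

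**What the plan says.** Protocol 6.2.b (Power and Sample Size) bases the HbA1c sample size on a two-sample t-test on the log scale, described as a "test between means, Bonferroni adjusted" at 0.05/3. It assumes "equal group variances" and "a baseline mean HbA1c of 6.5" percent, and concludes that "we will have 80% power to detect a 0.5% point difference in HbA1c with 92 patients/arm". It then states: "Accounting for a 20% attrition, this will require 115/arm, 345 patients total".

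The design has three arms. Section 6.1.a allocates them in blocks of six, "evenly distributed across the three study arms". Under Study Aim 1, "Primary outcomes and process measures will be compared between the three intervention arms (weekly, thrice-weekly, usual care"). The Aim 1 Statistical Analysis text adds that "the percent change from baseline will be compared across intervention arms using appropriate parametric (ANOVA", t tests) or a Wilcoxon method. Nothing makes the ANOVA a gate for the pairwise tests.

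The opening of 6.2.a sets significance at P<0.01, or with other multiplicity adjustments where applicable. It does not mention 0.05/3. No section says what the divisor 3 counts.

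**The concern.** Three arms give three pairwise contrasts: once-weekly against usual care, thrice-weekly against usual care, and thrice- against once-weekly. Bonferroni splits 5% equally over them and ignores that they are logically linked. Any two of the three nulls imply the third, so exactly two nulls can never be true together with the third false. A procedure that uses this link needs the strict level only for the first rejection.

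The trial's purpose in 1.1.a is to find the best feasible contact frequency. The hypotheses in 2.3 ask for both programmes against usual care and for thrice- against once-weekly. Such conclusions need more than one contrast, and that is where an equal Bonferroni split loses most.

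**Working it through.** **Inputs.** From 6.2.b: 92 per arm, 80% power, 0.5-point difference, level 0.05/3 = 0.0167 (printed as 0.016), 20% attrition. From 6.1.a: three arms, 1:1:1. Assumed: two-sided tests (sidedness is not stated). The SD is not stated and has to be back-solved.

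**The plan's own figures.** Attrition: 92/(1 − 0.20) = 115 and 3 × 115 = 345, both as printed. The 92 cannot be derived without an SD. Solving for the standardized effect:
- Normal approximation: d = (2.394 + 0.842) × √(2/92) = 0.477.
- Exact t: d = 0.481, so SD = 0.5/0.481 = 1.04 points on the raw scale. On the log scale the implied SD is 1.00 to 1.08, depending on whether the 0.5 is added to or taken from 6.5.
- Check: an SD of 1.0 with log(7.0/6.5) gives 91 per arm at 0.05/3 and 92 at 0.016.

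The comparison of procedures below depends only on d = 0.481, so the missing SD does not affect it.

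**Procedures.**
- Bonferroni: each contrast at 0.05/3.
- Shaffer: smallest p at 0.05/3; if rejected, the other two at 0.05. After a correct first rejection at most one true null remains, so 0.05/1 is enough.
- F-gate: global three-arm F-test at 0.05; if rejected, each pair at 0.05. The only intersection hypothesis is the global null, so this is a closed test.

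**Simulation.** 92 per arm, variance pooled over three arms, d = 0.481 for 0.5 points, 1,000,000 trials per scenario. Effects are HbA1c reductions (usual care, once, thrice).

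| Scenario and quantity | Bonferroni | Shaffer | F-gate |
|---|---|---|---|
| All equal: family error | 4.4% | 4.4% | 5.0% |
| (0, 0.5, 0.5): family error | 1.7% | 5.0% | 5.0% |
| (0, 0.5, 0.5): each programme vs usual care | 80% | 87% | 88% |
| (0, 0.5, 0.5): both beat usual care | 69.1% | 81.8% | 83.1% |
| (0, 0.25, 0.5): thrice vs usual care (0.5 points) | 80.3% | 81.6% | 82.9% |
| (0, 0.25, 0.5): once vs usual care, or thrice vs once (0.25 points) | 22% | 35% | 36% |
| (0, 0.5, 0.75): once vs usual care | 80% | 90% | 90% |
| (0, 0.5, 1.0): once vs usual care | 80% | 90% | 90% |

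With one arm very far away, the family error of Shaffer and of the F-gate stayed at 5.0%.

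**Rejections lost against Bonferroni.** Shaffer: none, by construction and in the simulation. F-gate: up to 0.39% of trials for a contrast, the largest value being for the extreme pair when the third arm lies midway.

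**Effect of P<0.01.** If each contrast were tested at 0.01, power for 0.5 points at 92 per arm would be 74 to 75%, below the planned 80%. Changing 6.2.b alone would therefore not secure the gain.

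**The case against.** The strongest reply is that the protocol never commits the analysis to Bonferroni. The word appears only in the sample-size text. Section 6.2.a leaves room for other adjustments, and sizing on a conservative level before testing with a sharper procedure is normal practice. This stands. A reader might infer that the three HbA1c tests are bound to 0.05/3 in the analysis, but the document does not say so. What remains is that 0.05/3 and P<0.01 are the only levels given, and neither makes use of there being exactly three arms.

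Second, the divisor 3 is unexplained. Section 6.2.b uses the same 0.05/3 for satisfaction, which 2.1.d compares between the two exercise arms only. There are also three aims, and 2.3.b lists three outcomes (HbA1c, VO2 max, physical activity). If the 3 protects outcomes or aims, a three-arm procedure cannot stand in for it: three independent families at 5% each would give 1 − 0.95³ = 14%. This stands as a condition on the point. For a t-test between arms on HbA1c, three contrasts is the most natural reading, but it is a reading.

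Third, the largest gain assumes that both frequencies work equally well, whereas 2.3.b expects thrice-weekly to do better. With once-weekly midway, the 0.5-point contrast gains only 1 to 3 points and the 0.25-point contrasts stay underpowered at 35 to 36%. This also stands, and it is why a range is given.

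Fourth, it would be tempting to call the gain free and the two procedures equivalent. Neither is exact: the F-gate misses a few Bonferroni rejections, Shaffer is slightly less powerful than the gate, and both lose matching simultaneous intervals.

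**Conclusion.** This is an inexpensive improvement in efficiency. Bonferroni is valid, and the documents do not support a reading that type I error is uncontrolled.

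At the planned 92 completers per arm, a closed procedure adds about 1 to 10 percentage points for a 0.5-point contrast. It adds about 13 to 14 points (69% to 82-83%) for showing that both programmes beat usual care when both lower HbA1c by 0.5. Family error stays at or below 5%.

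This rests on four assumptions: two-sided tests; a standardized effect of 0.481 (SD about 1.04, back-solved from the plan's own 80%); normality and equal variances, which 6.2.b already assumes; and a divisor of 3 that counts the arm contrasts. It holds for exactly three arms and does not carry over if an arm is added.

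**What to change.** - **6.2.b and Aim 1 (6.2.a):** state that the 3 refers to the three arm contrasts on HbA1c, and that they are tested by Shaffer's step-down: smallest p at 0.05/3 and, if rejected, the other two at 0.05.
- **Alternative:** a global three-arm F-test at 0.05 on the primary HbA1c model, then pairwise tests at 0.05 from that same model. This is slightly more powerful but misses a Bonferroni rejection in up to about 0.4% of trials. Choose one procedure before any outcome data are seen.
- **Opening of 6.2.a:** state that P<0.01 does not apply to these primary contrasts.
- **If the 3 was meant to cover several outcomes or aims:** say so and keep that adjustment. The step-down does not replace it.
- **Sample size:** keep N at 345 and present 80% per contrast as the conservative Bonferroni figure.

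The cost is wording only. The downside is that simultaneous confidence intervals no longer match the tests exactly. Report Bonferroni or Tukey intervals alongside, with a note that a contrast may be significant while its simultaneous interval includes zero.

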# **Chapter 1: Introduction to the IMPACT Research Study**

## 1.1 INTRODUCTION

### 1.1.a SUMMARY

The Initiate and Maintain Physical Activity in Clinics (IMPACT) Study is a research study utilizing physical activity in an intervention for Type 2 diabetes (T2DM) patients in a clinical setting. The study will compare structured group exercise within the clinic for T2DM patients compared to usual care, which does not involve structured group exercise within the clinic setting. The main purpose of the study is to determine the optimal and feasible level of frequency of structured contact needed in a clinical setting for adult T2DM patients to initiate and maintain physical activity recommendations long-term.

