#### **Clinical Effectiveness**

1. By the end of Phase 1, experimental study participants (Arm 1 & Arm 2) who adhered to their group exercise schedule should have greater improvements in primary outcomes compared to non-experimental study participants (Arm 3).
  - a. Improvements in primary outcomes include reduction in HbA1c levels, increase in VO2 max levels, and increase in self-reported physical activity levels.
2. By the end of Phase 1, experimental study participants who attended thrice-weekly group exercise sessions (Arm 2) should have greater improvements in primary outcomes compared to experimental study participants who attended once-weekly group exercise sessions (Arm 1).
3. By the end of Phase 2, experimental study participants (Arm 1 & Arm 2) who maintained their exercise schedule should have improved primary outcomes compared to non-experimental study participants (Arm 3).
4. By the end of Phase 2, experimental study participants who maintained thrice-weekly exercise sessions (Arm 2) should have greater improvements in primary outcomes compared to experimental study participants who maintained once-weekly exercise sessions (Arm 1).

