## **STUDY AIM 1: CLINICAL EFFECTIVENESS**

### **Research Questions**

1. Does a thrice-weekly, structured exercise regimen have greater reduction in HbA1c than a weekly contact exercise regimen? How do these interventions compare to usual care?
2. Are the same improvements observed for process measures (i.e., VO2 max and self-reported physical activity)?

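### One 0.5-point HbA1c difference sizes all three arm comparisons, though under the protocol's own ordering the three gaps cannot all be 0.5; a three-arm closed test would use the same patients better

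*Protocol*

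**What the plan says.** Protocol section 6.2.b describes the primary analyses as once versus thrice weekly, compared with usual care. For Aim 1 it names one test, "A two-sample *t*-test between means", on log HbA1c, with a Bonferroni alpha of 0.05/3 (printed as 0.016), and concludes: "we will have 80% power to detect a 0.5% point difference in HbA1c with 92 patients/arm". After 20% attrition this becomes 115 per arm and 345 in total. The divisor 3 matches the three pairs that three arms form. No other difference is given for any pair, and no pair is named as the one that 0.5 describes.

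The frequency contrast is prominent elsewhere. Section 1.1.a says: "The main purpose of the study is to determine the optimal and feasible level of frequency of structured contact needed in a clinical setting". The first research question of Aim 1 in section 6.2.a begins: "Does a thrice-weekly, structured exercise regimen have greater reduction in HbA1c than a weekly contact exercise regimen". Formally, though, the primary hypothesis (section 2.3.a) is exercise against usual care. Thrice versus once is a secondary hypothesis (section 2.3.b), under which thrice-weekly participants "should have greater improvements in primary outcomes compared to experimental study participants who attended once-weekly group exercise sessions (Arm 1"). The same list expects both exercise arms to beat usual care, and section 1.2.a calls once-weekly contact the minimum for a meaningful change in behaviour. The expected order is therefore usual care, once weekly, thrice weekly.

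Section 6.2.a separately sets significance at P < 0.01, or other multiplicity adjustments where applicable.

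**The concern.** A single detectable difference for every pair is common practice and harmless when nothing links the pairs. Here the expected ordering links them. The gap between thrice weekly and usual care is the sum of the other two gaps. If both component gaps were 0.5, thrice weekly would have to lower HbA1c by 1.0 point relative to usual care, a figure the protocol does not state. If instead the full gap is 0.5, an effective once-weekly arm leaves less than 0.5 for once versus thrice.

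At stake is how the frequency comparison is planned and read. It is the study's stated main purpose, it sits beside an 80% figure that may not apply to it, and it is tested with a Bonferroni split that is more conservative than three arms require.

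**Working it through.** **Inputs from Protocol section 6.2.b.** 92 evaluable per arm, equal arms, alpha 0.05/3 = 0.01667, power 80%, difference 0.5 points. **Assumed.** A two-sided test, since sidedness is not stated. The SD of HbA1c is not stated either and is back-solved.

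**Step 1: the plan's own figure.** With 92 per arm, 80% power at alpha 0.05/3 (exact noncentral t, 182 degrees of freedom) requires a standardised difference of 0.481. On the raw scale the implied SD is 0.5 / 0.481 = 1.04 points; on the log scale it is about 1.00 to 1.08, depending on how 0.5 points is converted. So 92 per arm cannot be derived from the stated inputs alone, but it is consistent with an SD near 1. The attrition step reproduces: 92 / 0.8 = 115, and 3 × 115 = 345.

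**Step 2: gaps add up.**

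(thrice vs usual care) = (thrice vs once) + (once vs usual care)

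With both terms on the right above zero, the three gaps cannot all be 0.5. Setting the left side to 0.5 makes thrice vs once less than 0.5 for any benefit of once weekly.

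**Step 3: power at smaller gaps.** The noncentrality is (gap / SD) × √(92/2), and the critical value is 2.416. Fixing 80% at 0.5 fixes the standardised scale, so these results depend essentially on the gap as a fraction of 0.5, not on the missing SD. Thrice vs usual care is held at 0.5. The shares credited to once weekly are illustrative and do not come from the protocol.

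| Once-weekly share of the 0.5 | Thrice vs once gap | Noncentrality | Power, alpha 0.05/3 |
|---|---|---|---|
| none | 0.50 | 3.26 | 80% |
| one third | 0.33 (exactly 1/3) | 2.17 | 41% |
| one half | 0.25 | 1.63 | 22% |
| 60% | 0.20 | 1.30 | 14% |

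With all 115 per arm evaluable, power at 0.25 is 28%. Reaching 80% at 0.25 would take about 364 evaluable per arm.

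**Step 4: the closed procedure for three arms.** Test all three arms together at the family level. If that test is significant, test each pair at the same level. With exactly three arms, any two pairwise equalities imply the third, so the only joint null is that all arms are equal. If all are equal, a false claim requires the overall test to reject. If exactly one pair is equal, only one true null is tested, at the family level. Familywise error is therefore controlled in both cases.

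Simulated with normal data, SD 1.04, 92 per arm, variance pooled over three arms (3 × 91 = 273 degrees of freedom) and thrice vs usual care at 0.5, power for once vs thrice is:

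| Gap | Bonferroni, family 0.05 | Closed, family 0.05 | Bonferroni, family 0.01 | Closed, family 0.01 |
|---|---|---|---|---|
| 0.33 | 41% | 57% | 22% | 32% |
| 0.25 | 22% | 36% | 9% | 16% |
| 0.20 | 14% | 25% | 5% | 10% |

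At the 0.05 family level, thrice vs usual care rises from 80% to 83-84%. Simulated familywise error stayed at the nominal level, within simulation error.

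**The case against.** The strongest reply is that nothing in section 6.2.b is false. It states a detectable difference, which holds for any pair that truly differs by 0.5, and it does not say that exercise versus usual care is expected to yield 0.5. Section 6.2.a also uses a 0.5% HbA1c reduction as a marker of individual success, so 0.5 may be a relevance threshold applied evenly to all pairs. This stands. A reader might infer that the stated 80% is wrong; the document does not support that.

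Nor does it support the inference that the trial could rarely show a once-versus-thrice difference. At a gap of 0.33 the power is 41%, and section 1.2.a points to a table of HbA1c change by exercise dose, not present in the text available here, which might support a larger gap. The additivity still holds: a 0.5 gap for once versus thrice plus any once-weekly benefit puts thrice weekly more than 0.5 ahead of usual care.

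The formal hierarchy also counts. Thrice versus once is a secondary hypothesis, all hypotheses are of superiority, and no equivalence claim is planned. A fear that a null result will be read as proof that once weekly suffices is therefore a caution about reporting and not a fault in the text.

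The percentages are for an unadjusted t-test, whereas section 6.2.a plans covariate adjustment and mixed models. If the correlation between baseline and outcome were 0.5 to 0.7 (assumed), power would be about 30-45% at a gap of 0.25 and 54-73% at 0.33: higher, but still below 80%.

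Finally, Bonferroni is valid, section 6.2.a leaves room for other adjustments, and the closed test leaves only 25-57% power at these gaps. All true. The closed test is an inexpensive improvement and does not cure the shortfall.

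**Conclusion.** The point holds as a limit on what the 80% covers. It is right for a pair truly 0.5 points apart, and under the protocol's own ordering not every pair can be. If thrice weekly beats usual care by 0.5 and once weekly has some benefit, once versus thrice has less than 80% power: 41%, 22% and 14% at gaps of 0.33, 0.25 and 0.20. This rests on the 0.5 being assigned to thrice versus usual care, on illustrative once-weekly shares, and on a two-sided unadjusted t-test with 92 per arm. It does not depend materially on the unstated SD.

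The Bonferroni split costs power that three arms need not give up. Within the same design and family level, the closed procedure adds about 11 to 16 percentage points for once versus thrice at 0.05, and about 5 to 10 points at 0.01.

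**What to change.** 1. In section 6.2.b, replace the Bonferroni split over three pairs with the closed procedure: an overall three-arm test at the family level, then each pair at that same level only if the overall test is significant.
2. State one family level and reconcile it with the P < 0.01 in section 6.2.a. The choice matters: at a gap of 0.25 the closed test has 36% power at a 0.05 family level and 16% at 0.01.
3. Say in section 6.2.b that the 80% applies only to a pair truly 0.5 points apart.
4. Report the once-versus-thrice estimate with its confidence interval, whatever the test result.

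The cost is wording and a change of test rule, with no added patients or data. There are two drawbacks. Pairwise claims then depend on the overall test being significant, and the closed test does not yield matching simultaneous confidence intervals as Bonferroni does, so the plan should say what kind of interval is reported.
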